# Effectiveness of the Essential Coaching Postpartum Digital Health Solution on Parenting Self-Efficacy, Mental Health, Well-Being, and Parenting Outcomes: Protocol for a Randomized Controlled Trial

**DOI:** 10.2196/78209

**Published:** 2025-10-17

**Keywords:** mobile health, mHealth, parents, SMS text message, postpartum

## Abstract

**Background:**

The transition to parenthood requires adjustments to new norms and expectations. While there is significant focus on the parenting transition for birthing parents (persons with a uterus), nonbirthing parents (parents who do not give birth, including fathers, gender-diverse parents, adoptive parents, or nongestational coparents) are less supported. Preventive education via SMS text messaging can fill a health service gap and provide timely, standardized, evidence-based information. The Essential Coaching Postpartum program includes 6 weeks of evidence-based daily SMS text messages on topics such as infant care, normal development, parental mental health, and self-care, with streams designed for birthing parents (Essential Coaching for Every Mother) and nonbirthing parents (Essential Coaching for Every Partner).

**Objective:**

The primary objective of this study is to compare the effectiveness of Essential Coaching Postpartum to standard care on parenting self-efficacy, mental health (ie, depression, anxiety, and stress), well-being (ie, general distress and sleep), and parenting outcomes (ie, relationship satisfaction and coparenting) among first-time nonbirthing parents in Nova Scotia, Canada. The secondary objective is to compare the effectiveness of Essential Coaching Postpartum to standard care among first-time birthing parents in Nova Scotia. The exploratory objective is to compare the effectiveness of Essential Coaching Postpartum to standard care among first-time parent dyads (ie, both birthing parent and nonbirthing parent) in Nova Scotia.

**Methods:**

This will be a randomized controlled trial. A total of 166 first-time birthing parents and 166 first-time nonbirthing parents from Nova Scotia will be recruited and randomly assigned to the intervention or control arm. The intervention arm will receive standard care plus the Essential Coaching Postpartum digital health solution, which consists of twice-daily SMS text messages in the first 3 weeks and daily messages in the next 3 weeks. The control group will receive standard care. Messages are personalized based on the infant’s age and the parent’s self-selected feeding preference (ie, breast or chest feeding, formula feeding, or combination feeding). The first message is sent on the second evening after birth, with parents being eligible to enroll up to 7 days post partum. Participants will complete questionnaires assessing parenting self-efficacy, mental health, well-being, and parenting outcomes at baseline (enrollment after birth), 6 weeks post partum (after the intervention), and 6 months post partum (follow-up).

**Results:**

Recruitment for this study started in June 2025 and is currently ongoing. As of September 15, 2025, 11 birthing and 5 nonbirthing parents have been recruited.

**Conclusions:**

We anticipate that providing parents with SMS text messages (ie, Essential Coaching Postpartum) during the 6-week postpartum period to complement standard care will improve parenting self-efficacy, mental health, well-being, and parenting outcomes.

**Trial Registration:**

ClincalTrials.gov NCT06996067; https://www.clinicaltrials.gov/study/NCT06996067

**International Registered Report Identifier (IRRID):**

PRR1-10.2196/78209

## Introduction

### Background

The transition to parenthood is a transformative period that requires physical, emotional, and social adjustments to new norms and expectations. While there is significant focus on the transition for birthing parents (persons with a uterus) [1], nonbirthing parents (parents who do not give birth, including fathers, sexual-minority parents, adoptive parents, or nongestational coparents) are less supported in the transition to parenthood [2,3]. Perinatal mental health and psychosocial adjustment challenges are common among both parents, which can have significant impacts on parenting relationships and child outcomes [4,5]. Higher parenting self-efficacy, defined as a parent’s perception of their ability to execute tasks associated with raising a child [6], has been associated with improvement in many outcomes for both parents and children, including lower parental anxiety and depression and fewer behavioral problems in children [7]. Even in uncomplicated pregnancies and births, parents may struggle with developing their parenting self-efficacy [8] and report anxiety and depression symptoms [9-12]. Poor parental mental health is known to be comorbid and can adversely impact the interparental relationship, leading to relationship dysfunction and negatively impacting child outcomes [13]. By contrast, high parental self-efficacy in one parent is associated with higher parenting self-efficacy in the other [14]. Thus, it is essential to identify ways to support all parents during the early postpartum period to improve individual, couple, and family outcomes.

In Canada, recommendations for postnatal care vary by province, with no standardization of care, education, or support across the country [15]. In Nova Scotia, the recommendations for birthing parents are to have a comprehensive postpartum assessment with their health care provider at approximately 6 to 8 weeks after birth [15]. While there is focus on family-centered care, there are no specific follow-up recommendations for the nonbirthing parent, leading to a significant gap in support. Families should be offered postpartum depression screening at 2 weeks post partum, 6 to 8 weeks post partum, and 4 months post partum [15]. However, this does not always occur in practice [16].

The lack of formal support during the postpartum period is a sharp shift from the intense monitoring that occurs near the end of pregnancy, when birthing people often meet with health care providers on a weekly basis [17]. After a person gives birth, this access to perinatal follow-up care is reduced significantly to only once or twice in the first year, with the primary assessment occurring typically at approximately 6 weeks post partum [18]. The amount and type of care a family receives post partum may depend on whether their obstetric care provider was a physician or a midwife, whether they have a primary care provider, whether they are considered to have high needs, or whether they have identified health concerns for themselves or their infant [15]. The care for a nonbirthing parent during this period is often nonexistent, with nonbirthing parents reporting feeling invisible to health care providers [19], leading to a gap in access to information and support during this critical period for new parents.

An innovative strategy that can be used to support parents is mobile health, defined as the use of mobile devices to transmit health content and services [20]. Parents already use their mobile phones to access internet-based information during the perinatal period [21,22]. SMS text messaging can be an ideal strategy for reaching and supporting parents because it allows access to information anytime, anywhere; moreover, the messages can deliver evidence-based information consistent with the infant’s developmental age [23]. Preventive education via SMS text messaging can fill a health service gap and provide timely, standardized, evidence-based information.

To address this need, our team developed and evaluated an SMS text messaging program, Essential Coaching for Every Mother, in which we demonstrated improved parenting self-efficacy and reduced postpartum anxiety in first-time birthing parents [24-26]. A limitation of the original program was that it focused only on birthing parents, excluding nonbirthing parents. Thus, we recently developed Essential Coaching for Every Partner to focus on nonbirthing parents, which complements the information provided in Essential Coaching for Every Mother by delivering evidence-based information directly to nonbirthing parents via SMS text messaging during the first 6 weeks of the postpartum period [27]. The Essential Coaching Postpartum program (inclusive of all types of parents) includes 6 weeks of evidence-based daily SMS text messages on topics such as infant care, normal development, parental mental health, and self-care and was designed in collaboration with parents and postpartum health care providers based on evidence-based information [28-31]. The goal of Essential Coaching Postpartum is not to replace face-to-face contact with health care providers but rather be an adjunct to standard care with specialized information targeting the unique needs of new parents. The aim of this study is to evaluate the effectiveness of Essential Coaching Postpartum on nonbirthing parents, birthing parents, and parent dyads in Nova Scotia.

### Objectives

The primary objective is to compare the effectiveness of Essential Coaching Postpartum with standard care on parenting self-efficacy, mental health (ie, depression, anxiety, and stress), well-being (ie, general distress and sleep), and parenting outcomes (ie, relationship satisfaction and coparenting) among first-time nonbirthing parents in Nova Scotia.

The secondary objective is to compare the effectiveness of Essential Coaching Postpartum with standard care on parenting self-efficacy, mental health, well-being, and parenting outcomes among first-time birthing parents in Nova Scotia.

The explorative objective is to compare the effectiveness of Essential Coaching Postpartum with standard care on parenting self-efficacy, mental health, well-being, and parenting outcomes among first-time parent dyads (ie, both birthing parent and nonbirthing parent) in Nova Scotia.

### Hypotheses

#### Primary Hypothesis

Our primary hypothesis is as follows: nonbirthing parents who receive Essential Coaching Postpartum will have higher parenting self-efficacy, better mental health (ie, lower scores for depression, anxiety, and stress), greater well-being (ie, lower distress scores and better sleep scores), and higher parenting outcomes (ie, higher relational satisfaction and coparenting) at 6 weeks post partum than those who receive standard care.

#### Secondary Hypotheses

Our secondary hypotheses are as follows: (1) birthing parents who receive Essential Coaching Postpartum will have higher parenting self-efficacy, better mental health, greater well-being, and greater parenting outcomes at 6 weeks post partum than those who receive standard care; (2) nonbirthing parents who receive Essential Coaching Postpartum will have higher parenting self-efficacy, better mental health, greater well-being, and greater parenting outcomes at 6 months post partum than those who receive standard care; and (3) birthing parents who receive Essential Coaching Postpartum will have higher parenting self-efficacy, better mental health, greater well-being, and greater parenting outcomes at 6 months post partum than those who receive standard care.

#### Exploratory Hypotheses

Our exploratory hypotheses are as follows: (1) parent dyads who receive Essential Coaching Postpartum will have higher parenting self-efficacy, better mental health, greater well-being, and greater parenting outcomes at 6 weeks post partum than those who receive standard care; and (2) parent dyads who receive Essential Coaching Postpartum will have higher parenting self-efficacy, better mental health, greater well-being, and greater parenting outcomes at 6 months post partum than those who receive standard care.

## Methods

### Study Design

A 2-group, parallel-arm randomized controlled trial (RCT) will be conducted to evaluate the effectiveness of Essential Coaching Postpartum on parenting self-efficacy, mental health (ie, depression, anxiety, and stress), well-being (ie, general distress and sleep), and parenting outcomes (ie, relationship satisfaction and coparenting) among first-time birthing and nonbirthing parents across Nova Scotia. The intervention will be compared to standard care that is currently being provided across Nova Scotia. This study follows a protocol similar to the original evaluation of Essential Coaching for Every Mother [32].

### Ethical Considerations

This study has been approved by the IWK Health Research Ethics Board (1031429) and is registered with ClinicalTrials.gov (NCT06996067). The CONSORT-EHEALTH (Consolidated Standards of Reporting Trials of Electronic and Mobile Health Applications and Online Telehealth) checklist [26] will be followed to enhance reporting quality for this eHealth intervention trial.

All participants will be asked to provide consent via REDCap (Research Electronic Data Capture; Vanderbilt University) [33], a secure web application for building and managing web-based surveys and databases, followed immediately by the baseline survey. Participants who do not complete the consent form or baseline survey will be considered to have withdrawn from the study.

To maintain confidentiality, all study data will be identified using a study number unique to each participant. Contact information will be collected via TextIt (Nyaruka) [34], a platform used to create and manage 2-way mobile messaging applications, which will be kept separate from survey data collected via REDCap to protect confidentiality.

To encourage survey completion, participants will be offered an honorarium for their time. Electronic gift cards worth CAD $5 (US $3.62) will be provided for each completed survey at baseline, 6 weeks post partum, and 6 months post partum. Participants who complete all 3 surveys will be entered into a draw for an electronic gift card worth CAD $250 (US $181.10). Four separate draws will be held: one each for the birthing parents in the control and intervention groups and one each for the nonbirthing parents in the control and intervention groups.

### Setting

This study will be conducted in Nova Scotia. In 2023, there were 6930 births in the province, with 3464 occurring in Halifax (primarily at IWK Health) [35]. There is a lack of standardized, universal postpartum support for new parents across the province. The Public Health Early Years program provides prenatal and postnatal support to all new parents giving birth in Nova Scotia. The *Loving Care* book series, developed by the Nova Scotia Department of Health and Wellness in partnership with Public Health Services, is offered after birth to provide information to new families about what to expect [28,29]. Families may also be offered a postnatal home visit with a nurse to provide support, including community and health referrals, guidance on infant care, and bonding. If more support is indicated, families are offered the enhanced home visiting program, which offers home visits from a community home visitor until the child turns 3 years of age [36]. Furthermore, 16% of people in the province do not have a primary care provider, resulting in a significant and growing number of newborns being referred to mobile “unattached newborn clinics” to receive care and support during the postpartum period [37,38].

### Patient Partnership

Four patient partners from diverse backgrounds and experiences as birthing and nonbirthing parents are involved in all aspects of planning, executing, and disseminating the work, following best practices in patient partnership.

### Eligibility Criteria

Participants will be recruited prenatally and postnatally. To pre-enroll prenatally, eligible birthing parents will (1) be pregnant (>28 wk) with their first child, (2) understand English, (3) have a mobile phone with SMS text messaging functionality and a data plan, and (4) live in Nova Scotia. Eligible nonbirthing parents will (1) have a pregnant (>28 wk) partner (ie, the birthing parent) expecting their first child or will be expecting their first child via an alternative method (eg, adoption or surrogacy), (2) understand English, (3) have a mobile phone with SMS text messaging functionality and a data plan, and (4) live in Nova Scotia. Participants who pre-enroll prenatally will only be considered enrolled and assigned a study number once they text “birth” to the study mobile phone number and are randomly assigned.

To enroll postnatally, eligible birthing parents will (1) be early postpartum (<7 d) with their first child, (2) understand English, (3) have a mobile phone with SMS text messaging functionality and a data plan, and (4) live in Nova Scotia. Eligible nonbirthing parents will (1) be early postpartum (<7 d) with their first child, (2) understand English, (3) have a mobile phone with SMS text messaging functionality and a data plan, and (4) live in Nova Scotia.

Participants (both birthing and nonbirthing parents) will be excluded if they (1) have a newborn who dies or is expected to die before leaving the hospital; (2) have no access to a mobile phone, either personal or shared; (3) are unwilling to receive SMS text messages; (4) decline participation or withdraw; or (5) participated in a previous iteration of this project (eg, development or evaluation). Parents are not required to participate as dyads to be inclusive of all family compositions; however, involvement of the other parent, if applicable, will be encouraged. Participants who do not fully complete the baseline survey will be considered withdrawn from the study. If the participant was randomly assigned to the intervention, they will continue to receive the messages, but no further data will be collected from them.

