### Screening and Baseline

Interested participants will complete a standardized SMS text message script for the eligibility screening process. During prenatal screening, participants will be assessed for preliminary eligibility, and those who qualify will be asked to text the study mobile phone number within 7 days of giving birth to be enrolled. At this stage, participants will be encouraged to provide their partner’s mobile phone number, if applicable, so that the partner’s interest can be assessed. Once a birthing person gives birth or enrolls post partum, they will complete additional screening questions to confirm eligibility.

After the birth of their child, all interested participants will complete the postpartum eligibility and randomization processes. During this stage, additional information will be collected, including the newborn’s name, date of birth, and feeding preference (ie, breast or chest feeding, formula feeding, or combination feeding). Participants will then be randomly assigned to the intervention or control group and asked to complete the consent form and baseline survey. If a parent dyad is participating, the nonbirthing partner will be sent an SMS text message after randomization to indicate their preferred type of feeding messages and to complete the consent form and baseline survey. Linked parent dyads will always be placed in the same intervention group. If dyad members complete the screening process separately and are inadvertently assigned to different groups, both parents will be moved to the intervention group.

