### Study Measures

Data will be collected from parents using self-reported web-based surveys administered through REDCap [33]. Table 1 outlines the timing of outcome collection. At baseline, demographics will be collected, including age, occupation, marital status, and educational level, as well as newborn information such as birth weight and delivery method. At 6 weeks post partum, a follow-up survey will be conducted to collect data on types of postpartum support sought and received, health concerns, and feeding behavior. All standardized questionnaires listed in Table 1 will be administered at baseline, 6 weeks post partum, and 6 months post partum.

**Table 1 table1:** Timing of measurement and outcome measurement questionnaires.

Outcome domains and variables			Outcome measure		Baseline (enrollment after birth)		After the intervention (6 wk postpartum)		Follow-up (6 mo postpartum)

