### Secondary Outcomes

Secondary outcomes will be collected using validated self-report measures, as follows:

Postpartum anxiety symptoms will be measured using the Postpartum Specific Anxiety Scale [42], a 51-item valid and reliable tool for assessing anxiety during the first 6 months post partum. A score of 112 or greater indicates clinical levels of anxiety [42].

Postpartum depression symptoms will be measured using the Edinburgh Postnatal Depression Scale [41]. A score greater than 9 (out of 30) suggests possible postpartum depression in both birthing and nonbirthing parents.

Postpartum stress will be measured using the Postpartum Childcare Stress Checklist [43], an 18-item scale assessing parental perceptions of childcare stress in the early postpartum period. Responses are summed to produce a score from 0 to 23, with higher scores indicating a higher level of postpartum childcare stress.

General distress will be measured using the Depression, Anxiety, and Stress Scale [44], a 21-item instrument that assesses the emotional states of depression, anxiety, and stress. Postnatal distress is classified by percentile scores, with total score (between 0 and 63) and a score for the three subscales (between 0 and 21), categorized into 5 severity ranges: normal, mild, moderate, severe and extremely severe, with higher scores indicated greater severity.

Sleep will be measured using the Patient-Reported Outcomes Measurement Information System (PROMIS) Short Form Sleep-Related Impairment (4a) and PROMIS Short Form Sleep Disturbances (4a) [45]. Sleep-related impairment measures perceptions of alertness, sleepiness, and tiredness during usual waking hours, as well as perceived functional impairments during wakefulness associated with sleep problems or impaired alertness. By contrast, sleep disturbance measures perceptions of sleep quality, sleep depth, and restoration associated with sleep. Higher scores indicate greater sleep-related impairment and disturbance.

Relationship satisfaction will be measured using the Couple Satisfaction Index [47], a 4-item scale assessing satisfaction in a relationship. Higher scores indicate greater satisfaction, whereas a score less than 13.5 is associated with notable dissatisfaction.

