Coparenting will be measured using the Brief Coparenting Relationship Scale [46], a validated 15-item instrument assessing 5 coparenting dimensions of agreement: closeness, child exposure to conflict, coparenting undermining, endorsement of partner’s parenting, and labor division [46]. Scores range from 0 to 60, with higher scores indicating greater coparenting.

We will also assess the implementation of Essential Coaching Postpartum using output data from the Twilio and TextIt platforms (eg, the number of SMS text messages sent, the number of SMS text messages delivered, error messages, unsubscription rates, and link clicks) as well as open-ended feedback from participants collected at 6 weeks post partum.

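### Unless the survey exempts them, the baseline-completeness rule withdraws eligible parents who have no partner or coparent, after randomisation and from every outcome

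*Protocol article*

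**What the plan says.** Five parts of the protocol article bear on this.

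- **Who is eligible.** Eligibility Criteria: "Parents are not required to participate as dyads to be inclusive of all family compositions". No criterion requires a birthing parent to have a partner, and none requires it of either parent type on the postnatal route. On the prenatal route, a nonbirthing parent needs a pregnant partner unless the child is expected by adoption, surrogacy or a similar path.
- **What is asked at baseline.** Study Measures: "All standardized questionnaires listed in Table 1 will be administered at baseline, 6 weeks post partum, and 6 months post partum". Table 1 includes the Couple Satisfaction Index-4 and the Brief Coparenting Relationship Scale. Secondary Outcomes describes them thus: "Relationship satisfaction will be measured using the Couple Satisfaction Index [47], a 4-item scale assessing satisfaction in a relationship" and "Coparenting will be measured using the Brief Coparenting Relationship Scale [46], a validated 15-item instrument assessing 5 coparenting dimensions".
- **The completeness rule.** Eligibility Criteria: "Participants who do not fully complete the baseline survey will be considered withdrawn from the study". Of such a participant in the intervention arm it says: "they will continue to receive the messages, but no further data will be collected from them". Ethical Considerations states the rule a second time: "Participants who do not complete the consent form or baseline survey will be considered to have withdrawn from the study".
- **When it bites.** Screening and Baseline: "Participants will then be randomly assigned to the intervention or control group and asked to complete the consent form and baseline survey".
- **How data are analysed.** Data Analysis specifies intention to treat, with analysis of covariance adjusted for the pretest score.

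**The concern.** Taken together, these statements let secondary questionnaires that may not apply to an admitted subgroup decide whether that subgroup contributes to the primary outcome. A single birthing parent or a single adoptive parent can answer the Karitane scale, but may have no meaningful answer to the 4 couple-satisfaction items, the 15 coparenting items, or both.

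Two things are at stake. If such a parent leaves items blank, the literal rule removes an eligible, randomised person from all outcomes because of a scale unrelated to the primary question. The self-efficacy result would then describe mainly parents with a partner or coparent, although the eligibility text says it is meant to include all family compositions. If the parent instead fills in the items to get through the form, the answers become pretest and outcome scores in the two couple analyses, where a couple-satisfaction score under 13.5 is read as marked dissatisfaction.

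This is separate from the order of randomisation, consent and baseline. The scales would be just as inapplicable if baseline came first, although the loss would then precede randomisation.

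**Working it through.** **Step 1: how the rule plays out.** The article does not describe how the REDCap survey is built or define full completion. There are three possibilities for a parent with no partner or coparent:

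1. Items can be left blank. The survey is then not fully complete, and the literal rule withdraws the parent.
2. Items are mandatory. The parent must give answers without meaning, and these enter the analysis.
3. Items are branched or have a not-applicable option. Nobody is lost. In that case the Study Measures sentence is not literally true for everyone, full completion has an unstated meaning, and the two couple outcomes are compared in a subset that the article does not declare.

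The first two cause harm. The third needs only clarification.

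**Step 2: the plan's own figure.** Inputs from Sample Size: 141 evaluable per parent type, 15% attrition, a 4-point difference, two-sided alpha 0.05, power 80%. Allocation is 1:1 (Randomization).

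141 / (1 - 0.15) = 165.9, rounded up to 166. The recruitment target is reproduced, and 166 - 141 = 25 places are allowed for attrition.

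**Step 3: implied SD.** The article does not give the SD, so the 141 cannot be checked independently. Solving the two-means formula (normal approximation, 70.5 per arm):

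SD = 4 / [(1.960 + 0.842) × √(2/70.5)] ≈ 8.48

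**Step 4: sensitivity.** Let s be the share withdrawn by this rule. The document gives no value, so s is assumed. If these losses come on top of 15% attrition:

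analysed N = 166 × (1 - s) × 0.85

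power = Φ(4 / [8.48 × √(2/(N/2))] - 1.960)

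| Assumed s | Withdrawn of 166 | Analysed | Power | Recruits needed to keep 141 |
|---|---|---|---|---|
| 0% | 0 | 141 | 80.0% | 166 |
| 2% | about 3 | 138 | 79.2% | 170 |
| 5% | about 8 | 134 | 78.0% | 175 |
| 10% | about 17 | 127 | 75.8% | 185 |

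If the withdrawals instead fall inside the 15% allowance, the attrition left for all other causes is 1 - 141 / [166 × (1 - s)]. That is about 13%, 11% and 6% for s = 2%, 5% and 10%.

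**Step 5: direction of the loss.** Partner status is fixed before randomisation, so the same kind of parent is removed from both arms. This route changes who is represented. It does not by itself unbalance the arms.

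**The case against.** The strongest reply is that the mechanism is inferred. The article never says that every item is mandatory, and branching is an ordinary form-building detail that a journal article may leave to the full protocol. The team plainly had absent partners in mind: marital status is collected at baseline, and involvement of the other parent and the request for a partner's number are both qualified as applying only where relevant. All this stands. A reader might infer that unpartnered parents cannot answer two questionnaires and are certain to be withdrawn. The text does not establish that.

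Two further points also stand. The scales are not one problem: a parent who has separated may still have a coparent and be able to answer the 15-item scale, leaving only the 4 couple items inapplicable. And the primary objective concerns nonbirthing parents, most of whom on the prenatal route have a pregnant partner, so the share affected there is probably small.

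The reply does not rescue the rule itself. The article states the rule twice, without exception, and states that all questionnaires go to everyone. Followed as written, it lets an inapplicable secondary scale end follow-up for the primary outcome. That is a rule badly fixed, not a detail left out.

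**Conclusion.** The point holds conditionally: unless the survey exempts parents without a partner or coparent, the rule as written removes them from the primary outcome or yields meaningless couple or coparenting scores. Either result runs against the stated inclusiveness, and removal also runs against intention to treat.

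The size rests on an assumed share of 2-10% lost in addition to 15% attrition, and on an SD back-calculated from the plan's own 141. On those terms power falls to about 79-76%, a modest loss. The share is probably towards or below the low end for nonbirthing parents and higher for birthing parents, who belong to the secondary objective.

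A reader might infer a biased comparison between arms or a seriously underpowered trial. Neither follows from this route. The harm is selective post-randomisation exclusion and a narrower population than the one declared. It is worth correcting because the correction is cheap and recruitment is at an early stage.

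**What to change.** 1. Amend the rule in both places, Ethical Considerations and Eligibility Criteria; changing only one would leave the article contradicting itself. A participant who has consented and has a baseline Karitane score stays in the study and is followed up. Missing or inapplicable secondary scales never trigger withdrawal.
2. In REDCap, branch the Couple Satisfaction Index on having a current partner, and the coparenting scale separately on having a coparent. If this is already done, say so and qualify the Study Measures sentence accordingly.
3. State that these two outcomes are compared among parents to whom the scale applies at baseline.
4. Analyse all other outcomes in all consented, retained participants. This should not be described as everyone randomised, because consent and the baseline Karitane scale both come after allocation.
5. State how a missing baseline covariate is handled, since the analysis of covariance adjusts for pretest scores and some secondary pretests will now be absent.

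**Cost.** The two couple outcomes have a slightly smaller denominator, and some secondary baseline scores will be missing. A minor amendment is needed during recruitment; by 15 September, 11 birthing and 5 nonbirthing parents had been enrolled. If branching already exists, the change is confined to wording.
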